---

## 1 Ethics

### 1.1 Independent ethics committee

It is the responsibility of the investigator to obtain approval of the study protocol, possible amendments and the written subject information and informed consent form from the IEC. The investigator should file all correspondence with the IEC.

### 1.2 Ethical conduct of the study

This study will be conducted in compliance with this protocol, applicable regulatory requirements, and in accordance with the ethical principles that have their origin in the Declaration of Helsinki).

### 1.3 Patient information and consent

Given the special epidemiological circumstances in which we find ourselves, we consider that the paper record of informed consent suggests additional risks of transmission of the COVID-19. For this reason, the protocol will be explained to the patient in front of a nurse who will act as a legal witness by signing the document on behalf of the patient.

Procedure:

1. Explain to the patient that he/she is proposed to participate in the study; his/her participation in the study is voluntary, his/her attendance will be carried out according to the usual protocols in force at each moment with the addition of anakinra or placebo according to the randomization.
2. Be informed of any procedures in addition to the usual care provided by the study protocol.
3. You will be informed that the study entails the inclusion of your anonymized clinical data in a database with the legally established levels of protection.
4. You will be informed that you have the right to withdraw from the study at any time, without giving any reason for doing so and without your medical care being affected.

- 
5. You will be expressly asked if you agree to participate in the study and your answer will be recorded in the note on the evolution of the EHR, with the expression the patient agrees to participate in the study

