## 4 Investigational plan

### 4.1 Overall study design and plan

This is a randomized, open-label, parallel group, 2-arm multicenter study to investigate the efficacy and safety of anakinra in reducing hyper-inflammation and respiratory distress in adult patients with severe COVID-19 and CSS pneumonia.

The study consists of screening, a 2-week treatment period and a 2-week follow-up period.

The 2-week treatment period is open, and the patients will be randomized to treatment with anakinra + standard of care or standard of care alone in a 1:1 ratio.

Anakinra will be administered as 4-times daily i.v. infusions for a maximum of 15 days (Days 1 to 15), according to the patient health status and expert clinical opinion. The primary endpoint will be evaluated at Day 15.

According to hospital internal protocol, if the patient improves enough to recommend his/her discharge before the 15th day of the study, the patient will be able to continue receiving the medication at home by s.c. administration (100mg/6 hours). In any case, follow-up visits by telephone or in person will be made, depending on where the patient is, until the end of the study.

The study duration for an individual patient will not exceed 4 weeks. The end of the study is defined as last patient last follow-up visit/phone call.

Figure 1:

[figure not shown]

The study design has a total sample size of 180 patients and consists of two stages. At the end of the treatment stage, the success rates are compared between each arm: anakinra + standard of care treatment vs standard of care alone.

A data review committee composed of experts in internal medicine will be involved in the study oversight and interpretation of the study results.

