## 4.4 Treatments

### 4.4.1 Treatments administered

According to the randomization schedule, patients in arm A will receive (IMP) and standard of care and patients in arm B will receive standard of care only, see Table 1.

The treatment standard of care will be based on hydroxychloroquine and/or lopinavir-ritonavir and/or azithromycin.

Table 1:

| Arm | Investigational product | Dosage form | Route         | Daily dose                                                                                           | Dosage regimen              |
|-----|-------------------------|-------------|---------------|------------------------------------------------------------------------------------------------------|-----------------------------|
| A   | Anakinra                | Solution    | i.v. infusion | Days 1-15: 400 mg/day in total, divided into 4 doses given every 6 hours                             | 4 times daily for 15 days   |
| A   | Hydroxychloroquine      | Tablets     | Oral          | Day 1-15: 400 mg/day in total, divided into 2 doses given every 12 hours (loading dose: 400 mg/12 h) | 2 times daily for 5 days    |
| A   | Lopinavir-Ritonavir     | Tablets     | Oral          | Day 1-15: 800/200 mg/day in total, divided into 2 doses given every 12 h                             | 2 times daily for 5-7 days. |
| A   | Azithromycin            | Tablets     | Oral          | Day 1-15: 500 mg /day                                                                                | 1 time daily for 5 days.    |
| B   | Hydroxychloroquine      | Tablets     | Oral          | Day 1-15: 400 mg/day in total, divided into 2 doses given every 12 hours (loading dose: 400 mg/12 h) | 2 times daily for 5 days    |
| B   | Lopinavir-Ritonavir     | Tablets     | Oral          | Day 1-15: 800/200 mg/day in total, divided into 2 doses given every 12 hours                         | 2 times daily for 5-7 days. |
| B   | Azithromycin            | Tablets     | Oral          | Day 1-15: 500 mg /day                                                                                | 1 time daily for 5 days.    |

---

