##### 4.4.2.1 *Anakinra*

The IMP anakinra is delivered as a sterile solution for injection, prefilled in a single-use syringe with the strength 100 mg. The total volume of injection is 0.67 mL and the concentration of anakinra in the solution is 150 mg/mL.

Anakinra must be stored at refrigerated conditions at 2-8 °C (36°-46°F) in a secure area at the study sites. Further instructions for handling and storage of the IMP anakinra are available in the IMP manual.

SOBI, will provide the study drug as well as the packing and distribution. Labeling will comply with national regulatory requirements.

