#### 4.4.3 Method of assigning patients to treatment groups

The different treatment groups are;

- Arm A: Anakinra as add-on to standard of care
- Arm B: Standard of care only

The ratio between the treatment groups is 1:1, i.e., the same number of patients will be randomized to anakinra or standard of care.

In order to assign each patient to each of the treatment branches and ensure a balance between them for the different centers, the method of random allocation by permuted blocks of sizes 10 and 12 will be used, using the randomizer library of the R statistical package, version 3.4.0.

Although the study is open, measures are taken to prevent a selection bias: one collaborator from each center will be in charge of the allocation, for which he will receive the identifying information of each recruited subject (trial identification number), attaching the branch indicated by the random procedure and returning this information to the people in charge of continuing the development of the intervention.

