#### 4.4.6 Blinding and unblinding

This is an open study with no level of blinding.

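### The consent procedure in section 1.3 names a placebo that this open-label trial does not have, so the prescribed oral explanation misdescribes the control arm

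*Protocol*

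**What the plan says.** Protocol section 1.3 replaces the usual paper record of consent with an oral explanation given in front of a nurse, who signs for the patient. It lists five steps. Step 1 covers what the patient is being asked to join, and describes the randomised treatment as usual care "with the addition of anakinra or placebo according to the randomization".

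The design sections describe a different control:

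- Section 4.1: "This is a randomized, open-label, parallel group, 2-arm multicenter study", in which "the patients will be randomized to treatment with anakinra + standard of care or standard of care alone in a 1:1 ratio".
- Section 4.4.1: "patients in arm B will receive standard of care only". The arm B rows of Table 1 list hydroxychloroquine, lopinavir-ritonavir and azithromycin, and no placebo.
- Section 4.4.2.1: "The IMP anakinra is delivered as a sterile solution for injection, prefilled in a single-use syringe with the strength 100 mg". No other product is described under section 4.4.2.
- Section 4.4.3: "Arm B: Standard of care only".
- Section 4.4.6: "This is an open study with no level of blinding".

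**The concern.** The control condition is a central fact for someone with severe pneumonia deciding whether to be randomised. The word placebo suggests that every participant receives something in addition to usual care. By inference, it also suggests that participants will not know which addition they received. In this trial neither is so: arm B receives nothing added, and everyone knows the allocation.

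The place of the phrase matters. It is in a numbered procedure, not in background text. Section 1.2 says the study will be conducted in compliance with the protocol. Section 7.4 tells investigators not to deviate except to remove an immediate hazard, and it prohibits waivers. Read literally, an investigator who follows step 1 describes the wrong control arm, and one who describes the right control arm departs from the protocol.

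The oral explanation also carries unusual weight. The nurse signs on the patient's behalf, and under step 5 the clinical record notes only that the patient agrees to take part. The patient's own signature is not there as a second check on the spoken description.

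**Working it through.** No arithmetic applies, because the point is a contradiction in the text. The check sets the consent wording against each section that defines the arms, the product, the allocation and the blinding, and then looks for any other provision for a placebo.

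| Item | Section 1.3, step 1 | Design sections |
|---|---|---|
| Control treatment | Usual care plus placebo | Standard of care alone (4.1, 4.4.1, 4.4.3) |
| Products supplied | Anakinra and, by implication, a placebo | Anakinra only (4.4.2.1) |
| Knowledge of allocation | Not stated; a placebo suggests it is concealed | Open, no blinding (4.1, 4.4.6) |

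1. **Could both descriptions be true?** No. A patient in arm B either receives a placebo or receives standard of care only. Table 1 lists what arm B receives, and placebo is not in it.
2. **Is a placebo provided for anywhere else?** No. The word appears in two other places, both about other trials: the sepsis results cited in section 2.1 and titles in the reference list in section 11. No placebo product, preparation or administration is described for this study.
3. **Which side is the error on?** The design sections agree with one another on every item. The consent phrase stands alone, so it is the wrong one.
4. **Is it superseded text or an extraction fault?** No. It is a complete sentence in the current body of the protocol, and not part of an amendment log.
5. **Does any calculation depend on it?** No. The 180 patients (90 per arm), the assumed success rates of 88% and 92%, the 0.05 significance level and the chi-square comparison do not use a placebo or blinding as an input.

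**The case against.** The strongest objection is that this is one wrong word, perhaps left over from a template, and that patients may have been told the right thing anyway. Section 1.1 requires ethics committee approval of written subject information and a consent form, and sections 4.3.1 and 4.5.1.2 require written, signed consent. Those documents are not available here and may describe the control correctly. Section 1.3 also says that the protocol itself is explained to the patient, and its design sections are right. Step 1 summarises what to explain and is not a verbatim script.

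Most of this stands. A reader might infer that every participant was misinformed, or that consent was given to a trial that does not exist. The documents do not support that: they show what the procedure prescribes, not what was said at the bedside or printed on the form. The objection does not remove the error from the procedure that staff are told to follow.

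A reader might also infer a statistical consequence: control patients who expected a placebo would withdraw more often and so bias the comparison. The documents do not support this either. In any open-label trial, control patients learn that nothing is added, and correcting the wording would not change that. No withdrawal rate for this cause is given, and any figure would be invented. Nor can withdrawals be set against the planned difference in success rates, because a withdrawal is not an outcome event. Section 4.3.3.1 keeps patients who stop study treatment in the study, and section 6.1 already allows for a 10% loss.

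**Conclusion.** The contradiction is certain and should be corrected. Section 1.3 has patients told of a placebo control, while sections 4.1, 4.4.1, 4.4.2.1, 4.4.3 and 4.4.6 describe an open-label comparison with standard of care alone. It is an internal contradiction, not a criticism of the design choice.

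In extent it is one phrase, in a step that would apply to each of the 180 planned patients. Its importance rests on participant information alone. Sample size, type I error and the planned analysis are unaffected, and no bias in the trial's result has been shown.

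The conclusion needs no numerical assumption. What cannot be settled from the protocol is whether the written information sheet and consent form carry the same wording. That the word placebo would lead a patient to expect blinding is an inference, since section 1.3 does not mention blinding.

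**What to change.** Reword step 1 of section 1.3 so that it agrees with sections 4.1, 4.4.1, 4.4.3 and 4.4.6. It should say that the patient will be randomised to anakinra in addition to standard of care or to standard of care alone, and that patient and clinicians will know which. Check the information sheet and the consent form for the same wording and correct them if needed.

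The cost is a change to one sentence and a short amendment. Under section 1.1, amendments and the consent form need ethics committee approval, so a notification would not be enough. No treatment rule, sample size or analysis changes. If anyone has already consented under the present text, which the protocol does not show, the submission should say so, so that the committee can decide whether those patients need a corrected explanation.

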#### 1.4 Data protection

1. Participants will be assigned a unique identifier by the investigator. Any participant records or datasets that are transferred to the sponsor will contain the identifier only; participant names or any information which would make the participant identifiable will not be transferred.
2. The participant must be informed that his/her personal study-related data will be used by the sponsor in accordance with local data protection law. The level of disclosure must also be explained to the participant.
3. The participant must be informed that his/her medical records may be examined by Clinical Quality Assurance auditors or other authorized personnel appointed by the sponsor, by appropriate IRB/IEC members, and by inspectors from regulatory authorities.

---

## 2 Introduction

### 2.1 Background

This protocol has been prepared by the Systemic Autoimmune Diseases Group (GEAS) steering committee from the Spanish Society of Internal Medicine (SEMI) in response to the current urgent situation that we are living in Spain because of the COVID-19 pandemic. The GEAS member are experts in the treatment of autoinflammatory diseases and the use of biologic drugs in general, and anakinra in particular. importantly, in Spain, internal medicine physicians are currently involved in the treatment of patients infected with SARS-CoV-2.

The objective of this study is to investigate new possibilities to reduce the number of patients requiring mechanical ventilation. This is intended to address the most urgent need to preserve the access to intense care unit support to the lower possible number of patients and may potentially reduce mortality.

In December 2019, a respiratory condition caused by what was later identified as a new coronavirus (SARS-CoV-2) was detected in Wuhan Province, China (1). In these four months, the virus has spread throughout the world's population, in more than 100 countries and affecting thousands of people. The WHO declared in March that we were facing a pandemic because of this virus, in which Europe could now be considered the epicenter. The strict containment measures implemented in China, the mass detection of the virus with subsequent isolation of cases and contacts that has been carried out in countries such as Singapore, Taiwan or South Korea seem to have been useful in limiting the virus' spread. Consequently, in our country, and given the extension of the infection, a state of alarm has been decreed, at least for four weeks. Despite the containment measures, numerous cases are still being diagnosed every day, with an approximate lethality of 3.7%, especially in those considered at risk such as patients over 60 years of age and with comorbidities (Report nº 17. COVID-19 situation in Spain on 27 March 2020. COVID-19 team. SiViES. CNE. CNM. ISCIII).

When SARS-CoV-2 infects the respiratory tract, it causes the disease called COVID-19. From the point of view of the natural evolution of the disease, this can be a mild respiratory syndrome, which will occur in approximately 80% of cases, or a more serious disease, with the appearance of pulmonary infiltrates and in some patients a respiratory distress with rapidly progressive worsening (2). This second phase, which is only reached by a subgroup of

patients, is usually seen in the interval between day 7 and day 10 of the infection from the onset of symptoms. So far, there is no proven explanation for this great variability in its clinical expression.

The treatment used in our country so far is based on the combination of hydroxychloroquine, azithromycin and antiretrovirals (protease inhibitors, lopinavir), based on previous experiences. Several clinical trials are currently underway in Spain: PanCOVID-19 (Azithromycin + Hydroxychloroquine + lopinavir/ritonavir), GS-US-540-5774 (Remdesivir), EFC16844 (Sarilumab) and WA42380 (Tocilizumab) as well as international projects such as Discovery (NCT04315948), Solidarity and REMAP-CAP which include other treatment alternatives such as interferon-beta-1B or Anakinra.

According to recent data from the Chinese cohorts, a subgroup of patients with COVID-19 shows a very marked increase in inflammatory test data, such as lymphopenia, thrombocytopenia, C-reactive protein (CRP) levels, lactate dehydrogenase (LDH), IL6 ( $> 40$  pg / mL) and D-dimer ( $> 0.28$   $\mu$ g / L), the latter two being predictive of the development of severe pneumonia (sensitivity 93.3%, specificity 96.4%) (2,3,4). Accumulating evidence suggests that a subgroup of patients with severe COVID-19 might have a cytokine storm syndrome (CSS). In this group of patients in which this "inflammatory profile" is detected, the damage observed is not a direct consequence of the viral infection (viral necrotizing pneumonia) but rather a secondary hyperimmune response, mainly related to the monocyte/macrophage activation, which has also been observed in autopsy studies and previously in other infections by other types of coronavirus (5,6). This CSS is superimposable to that observed in patients with secondary hemophagocytic lymphohistiocytosis (sHLH), often triggered by viral infections or macrophage activation syndrome (MAS), secondary to systemic and autoinflammatory autoimmune diseases.

In this group of patients there is a significant release of pro-inflammatory cytokines, including interleukin (IL) -1 $\beta$  and IL-6 (6). Of these, IL-1 $\beta$  has a greater pathogenic relevance, given that it promotes the inflammatory cascade and also induces the synthesis of several inflammatory genes such as IL-6 itself, IL-8, MCP-1, COX-2, I $\kappa$ B $\alpha$ , IL-1 $\alpha$ , IL-1 $\beta$  and MKP-1. Numerous case reports and case series have been published supporting the use of IL-1 $\beta$  blockade in the MAS (8-12). At this time, there is some experience in the treatment of COVID-19 in the subgroup of patients in the inflammatory phase with Tocilizumab (IL-6 receptor blocker), but

no controlled studies have been completed as yet. However, IL-6 is not a key molecule in the cytokine storm that triggers MAS (9).

Anakinra (IL-1Ra) is a recombinant IL-1 receptor antagonist with a very short half-life of 4-6 hours, requiring a daily subcutaneous injection of a 100 mg dose. It has also been shown to reduce levels of other pro-inflammatory cytokines (including IL-6 and IL-18) and acute phase reactants such as PCR and ferritin. Therefore, it has been used in the control of autoinflammatory syndromes and in patients with MAS (7,8). In addition, data have been reported from a phase 3 randomized controlled trial of IL-1 blockade with anakinra in sepsis with characteristics of MAS, which showed a significant improvement in the 28-day survival rate (65.4% anakinra vs. 35.3% placebo), with HR for death 0.28 (0.11-0.71,  $p = 0.0071$ ), with no increased adverse events (11).

## 2.2 Study rationale

As shown by the data available in the most recent literature generated from the Chinese experience, and by the most recent data made available by the different Spanish hospitals responsible for the management of these patients, hyper- inflammation, caused by a cytokine storm resulting from an exaggerated response of the immune system to the presence of the virus (CSS-like pneumonia), is considered to represent one of the most important negative prognostic factor in patients infected with SARS-CoV-2. The inclusion criteria for COVID-19 used in this protocol is based on the analysis of routine blood chemistry data obtained from patients with SARS-CoV-2 infection. This criterion has been designed with high sensitivity (>90%) for patients who require ICU admission (12). This constitute the rationale for testing drugs specifically targeted to reduce the cytokine storm.

This protocol has been prepared for the purpose of addressing the current medical emergency, given the severity of the disease and the extremely high number of individuals affected. The objective of this study is to investigate anakinra to reduce the number of patients requiring mechanical ventilation. This is intended to address the most urgent need to preserve the access to intense care unit support to the lower possible number of patients and may potentially reduce mortality.

### 2.3 Potential risks and benefits

The potential applicability of the results of this clinical trial, in an extraordinary health emergency such as COVID-19, is obvious. Positive results could help to define the standard treatment of severe COVID-19 pneumonia and have a dramatic impact on both local and global morbidity and mortality. Negative results would constitute very useful scientific evidence for abandoning unfounded empirical approaches and would help redirect resources and efforts in another more promising direction. The expected length of time needed for recruitment is 3-4 weeks, depending on the epidemiological progression of the pandemic in our centers, so results could be available in early May 2020.

Anakinra is a recombinant form of the human IL-1Ra, r-metHuIL-1Ra, which is produced by recombinant DNA technology in an *E. coli* expression system. Therapeutically, anakinra neutralizes the biological activity of IL-1 (IL-1 $\alpha$  and IL-1 $\beta$ ) by competitively inhibiting its binding to the IL-1RI.

Kineret (anakinra) was first approved for treatment of RA in the US in 2001 and subsequently in the EU/EEA in 2002. In 2012, an sBLA on anakinra for treatment of NOMID was approved in the US. Kineret is also approved for treatment of CAPS (in EU/EEA, Israel and Australia), Still's disease, including SJIA and AOSD (in EU/EEA) and SJIA (in Australia).

The initial IND for anakinra was granted in 1991. The estimated cumulative exposure to anakinra in completed company sponsored clinical studies up to 1 May 2018 is 6404 subject-years, in 8518 subjects with various indications. Anakinra is administered s.c. at doses of 100 mg/day (RA) or in weight-based doses of up to 8 mg/kg/day (NOMID). In clinical studies in sepsis, doses up to 2 mg/kg/hour i.v. over 72 hours were administered to >500 patients and were well tolerated. For additional information of i.v. administration of anakinra, see Section 5.4.4.1.

